## Abstract

Tai Chi has been proven to be a safe and effective assistant therapy for healthcare and disease treatment. However, whether the adjuvant therapeutic effect of Tai Chi is general or disease-oriented remains uncertain. This trial focuses on exploring the specific and nonspecific effects of Tai Chi and its potential central responses. The results will deepen our understanding of the characteristics of Tai Chi exercise for adjuvant therapeutic effects and promote its application in the clinic. In this neuroimaging trial, 40 functional constipation (FC) patients and 40 healthy subjects (HS) will be recruited and will receive 10 weeks of Tai Chi exercise. The motor function, respiratory function, stool-related symptoms, quality of life, and emotional state of the participants will be evaluated at the baseline, the 5-week Tai Chi practice, and the end of practice. The potential changes in the heart rate variability and the cerebral function will be recorded by the 24 h dynamic electrocardiogram at the baseline and the functional magnetic resonance imaging at the end of practice. The possible correlations among the clinical variables, the heart rate variability, and the cerebral activity alterations in FC patients and HS will be analyzed. The healthcare and therapeutic effects of Tai Chi exercise might consist of the specific and nonspecific effects. This study provides not only a new perspective for understanding Tai Chi but also a new approach for investigating the mind-body exercise. This trial was registered in the Chinese Clinical Trial Registry (http://www.chictr.org.cn/showproj.aspx?proj=33243) on 28 November 2018 (registration number: ChiCTR1800019781; protocol version number: V1.0). This trial is currently in the stage of recruiting patients. The first patient was included on 1 December 2018. To date, 18 FC patients and 20 HS have been included. Recruitment will be completed in December 2020.

## 1. Introduction

Tai Chi is a traditional mind-body exercise, which originated from ancient China and widely spread all over the world. It is reported that there are 5 and 150 million Tai Chi practitioners in China and the whole world, respectively. Tai Chi has dual effects on healthcare and treatment. For healthy subjects (HS), the healthcare effects of Tai Chi in strengthening muscle strength [1], improving physical flexibility [2], enhancing the ability to balance and control [2], increasing vital capacity [3], reducing stress [4], and others have long been identified. For patients, the therapeutic effects of Tai Chi for treating multiple chronic diseases including osteoarthritis [5], hypertension [6], type 2 diabetes mellitus [7], coronary heart disease [8], and chronic obstructive pulmonary disease [9] have also been proven by a number of studies. These studies indicated that Tai Chi was widely involved in the prevention, treatment, and rehabilitation of various diseases. Does Tai Chi have different effects on the same organ/system in different practitioners? For example, a systematic review and meta-analysis showed that mind-body interventions, including Tai Chi, were effective in alleviating gastrointestinal symptoms and improving the quality of life (QOL) of patients [10]. Does Tai Chi have different gastrointestinal modulation effects between patients with gastrointestinal disorders and HS? In other words, is the gastrointestinal regulation of Tai Chi disease-oriented and influenced by individual physical condition? However, majority of the Tai Chi-related studies were performed either on patients or HS, and few studies were performed on both patients and HS to investigate the influence of physical conditions on the effect of Tai Chi.

On the basis of the characteristics of Tai Chi and previous researches, we predict that the effects of Tai Chi include two aspects: the relatively specific effects and nonspecific effects. The nonspecific effects mainly refer to the modulating effects on human motor function (muscle strength, physical flexibility, etc.) and respiratory function, especially vital capacity. The nonspecific effects might also manifest as maintaining the normal function of organs/systems, keeping the body in a relatively balanced and coordinated state. While the relatively specific effects of Tai Chi are disease-oriented, meaning that when the body is in a pathological state, Tai Chi practice might reduce the hyperactive function to improve the hypoactive function.

To test the hypothesis, we design this neuroimaging study. In this study, both functional constipation (FC) patients and HS were selected as participants to investigate the specific effects (gastrointestinal function) and nonspecific effects (motor function and respiratory function) of Tai Chi. FC is a common functional gastrointestinal disorder (FGID) with high prevalence. It is characterized by various constipation-related symptoms, including reduced defecation, defecation stress, hard stools, and uncomfortable abdominal muscle in the absence of evident organic or structural reasons for these symptoms. A randomized control trial indicated that Tai Chi practice could significantly improve the constipation symptom of patients with chronic FC [11].

This study aims to (1) investigate the nonspecific effects of Tai Chi by comparing the influence of Tai Chi practice on motor function and respiratory function between FC patients and HS using the lower-extremity muscle strength test, functional balance tests, and vital capacity test; (2) investigate the specific effects of Tai Chi from three aspects, including gastrointestinal symptom, autonomic nervous activity, and emotional state; and (3) explore the potential central responses of Tai Chi's specific and nonspecific effects by functional magnetic resonance imaging (fMRI).

## 2. Methods and Analysis

### 2.1. Study Design

The trial is designed as a neuroimaging trial that focuses on specific and nonspecific effects of Tai Chi and its potential central responses. A total of 40 FC patients and 40 HS will be recruited. Fifteen participants in each group will be randomly selected to undergo MRI scan. The study procedure is outlined in Figure 1.

### 2.2. Sample Size Calculation

We will investigate the therapeutic effects of Tai Chi for FC patients. According to our preliminary study from which we recruited 10 FC patients with the Tai Chi intervention, the mean improvement of weekly complete spontaneous bowel movements (CSBMs) of Tai Chi was 1.67 ± 0.89 times. A systematic review [12] focusing on the management of FC reported the mean improvement of weekly CSBMs of polyethylene glycol (the first-line medication of FC) was 1.8 times. We hypothesize that the therapeutic effects of Tai Chi are not less than the polyethylene glycol. Considering *α* = 0.05, 1 − *β* = 0.8, the study design required a sample size of 36 for each group with the one-sample noninferiority test [13], with a drop-out rate of 10%. A total of 40 patients with FC and 40 HS will be finally recruited.(1)$$\begin{array}{c} N={\left(\sigma \frac{Z_{1-\alpha }+Z_{1-\beta }}{\mu -\mu o-\delta }\right)}^{2}. \end{array}$$

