### 2.10. Statistical Analysis

#### 2.10.1. Clinical Data Analysis

Clinical data will be analyzed by independent statisticians who do not know the test procedure based on the principles of intention to treat (ITT) and per protocol. The statistical significance threshold has *p* value <0.05. The results of the participants who failed to complete the study will be considered no different from the baseline data in ITT analysis. All continuous variables will be presented as mean ± standard deviation. The categorical variables will be described in percentage (%). The clinical data in the two groups (FC group and HS group) will be compared with two-sample *t*-tests, and the comparisons of the baseline and after intervention in each group will be compared with a paired sample *t*-test. Nonparametric tests (Mann–Whitney *U* test) will be used to compare nonnormally distributed clinical data, and the *χ*^2^ test or Fisher's test will be used to compare categorical variables.

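### The 36 per group at 80% power come from a one-sample noninferiority test that applies only to FC patients, has no stated margin and matches none of the analyses listed in section 2.10.1

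*Protocol article*

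**What the plan says.** All of the sizing is in section 2.2 of the protocol article. The hypothesis is "We hypothesize that the therapeutic effects of Tai Chi are not less than the polyethylene glycol". The inputs are a pilot of 10 FC patients, in whom "the mean improvement of weekly complete spontaneous bowel movements (CSBMs) of Tai Chi was 1.67 ± 0.89 times", and a review figure, by which "the mean improvement of weekly CSBMs of polyethylene glycol (the first-line medication of FC) was 1.8 times". The error rates are given as "Considering *α* = 0.05, 1 − *β* = 0.8". The printed formula is for a single mean and uses the one-sided normal quantile for alpha. It contains a margin δ, which is given no value. The conclusion is "the study design required a sample size of 36 for each group with the one-sample noninferiority test", raised to 40 FC patients and 40 HS for 10% drop-out.

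Section 2.10.1 names the clinical tests. FC and HS are compared by two-sample t-tests, and "the comparisons of the baseline and after intervention in each group will be compared with a paired sample" t-test. Mann–Whitney, χ² and Fisher tests are also listed. The threshold is p below 0.05, with no sidedness given.

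The Introduction lists three aims. The first is pursued by "comparing the influence of Tai Chi practice on motor function and respiratory function between FC patients and HS". The second includes gastrointestinal symptoms, to which CSBM change belongs. None of the three mentions polyethylene glycol. Section 2.4.2 excludes HS who have gastrointestinal symptoms or signs.

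**The concern.** A sample size carries a power statement for one particular test. Here that test asks whether the FC mean change lies above 1.8 minus a margin. This raises three problems.

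- **Group.** The test involves only FC patients. HS are selected to have no gastrointestinal symptoms, so improvement in constipation is not a hypothesis about them. Half of the trial is sized by a calculation that does not apply to it.
- **Margin.** The pilot mean is 0.13 below the reference, so the design works only with a margin larger than 0.13, and the required number changes steeply with it. It is the one input that a reader cannot find.
- **Analysis.** The list in section 2.10.1 has no one-sample test, no confidence bound and no comparison with 1.8.

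A reader is likely to take the 80% as the power of the FC-HS comparisons, which it is not. A later noninferiority statement would have neither a published margin nor a listed test behind it.

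**Working it through.** **Inputs from section 2.2:** μ = 1.67, σ = 0.89, μ0 = 1.8, α = 0.05 (one-sided, as the formula is printed), power 0.80, drop-out 10%. δ is not given.

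**1. The plan's own figure.** N = [σ(Z₁₋α + Z₁₋β)/(μ − μ0 − δ)]². The quantiles sum to 1.645 + 0.842 = 2.486, and μ − μ0 = −0.13. Without δ, N cannot be computed. Solving for N = 36:

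- 0.89 × 2.486/√36 = 0.369
- |δ| = 0.369 + 0.13 = 0.499

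Putting in a margin of 0.5 (δ = −0.5) gives (0.89 × 2.486/0.37)² = 35.8, so 36, and 36/0.9 = 40. The plan's figures are reproduced. Any margin from 0.499 to 0.504 rounds up to 36, so a value of about 0.5 was presumably used.

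**2. How much rests on the margin** (same formula, one-sided 0.05, normal approximation):

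| Margin (CSBM/week) | N for 80% power | Power at n = 36 |
|---|---|---|
| 0.3 | 170 | 31% |
| 0.4 | 68 | 57% |
| 0.5 | 36 | 80% |
| 0.6 | 23 | 94% |

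This shows why the margin has to be disclosed. It does not show that 36 is wrong for the margin that was used.

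**3. The tests that section 2.10.1 lists.** Two-sided 0.05 is assumed, since no sidedness is given; power is from the noncentral t distribution.

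- *FC versus HS, two-sample t-test, 36 per group.* The normal approximation gives a detectable difference of (1.960 + 0.842) × √(2/36) = 0.66 SD at 80% power; the t distribution gives 0.67 SD. At a difference of 0.5 SD the power is 55%.
- *Paired t-test in 36 FC patients.* The normal approximation gives (1.960 + 0.842)/√36 = 0.47 SD at 80% power; the t distribution gives 0.48 SD. The pilot change is 1.67/0.89 = 1.88 SD, where power is close to 100%.

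The stated 80% is thus not the power of either test at the effect used in section 2.2.

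**4. Precision.** For 36 FC patients with SD 0.89, the 95% half-width for the mean change is t(0.975; 35) × 0.89/√36 = 2.030 × 0.1483 = 0.30 CSBM/week.

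**The case against.** The strongest reply is that nothing is miscalculated: with a margin of 0.5 and the one-sided 0.05 that the formula prints, both 36 and 40 come out exactly. That stands. The fault is an undisclosed input and a mismatch with the analysis, not an arithmetic error.

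A second reply is that this is a journal article, and that the full protocol or an analysis plan may give the margin and the noninferiority test. That stands in part. One can say that section 2.10.1 does not name the test, not that it will never be run. But the article prints the formula with every other input and names its own list of tests, so the mismatch lies within the article. No further document could make a one-sample FC calculation apply to HS.

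Four stronger readings may tempt a reader, and the article does not support them.

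- *That the margin would be chosen after the data.* The number 36 itself points to a margin of about 0.5 fixed in advance.
- *That one-sided 0.025 should have been used.* The formula states one-sided 0.05, and nothing in the article requires another level.
- *That 36 is too few.* The paired FC analysis, which serves the gastrointestinal part of the second aim, is amply powered at the pilot values. Section 3.1 expects the nonspecific benefits in patients and HS alike, so power to detect an FC-HS difference is not clearly the right yardstick for the first aim.
- *That the fixed 1.8 is itself an error.* Any one-sample test has a fixed reference, and the source is disclosed. It limits the interpretation only.

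**Conclusion.** The point holds as a mismatch between sample size and analysis. The stated 80% power belongs to a one-sample noninferiority test in FC patients. That test says nothing about HS, has no stated margin and is not among the analyses in section 2.10.1.

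For the listed tests, 36 per group means 80% power at about 0.67 SD between groups and at about 0.48 SD for the paired FC change. These figures assume two-sided 0.05, roughly normal data and 36 evaluable participants per group. The margin of about 0.5 CSBM/week, with its null mean of about 1.3, is inferred from the result. It should not be treated as the sponsor's documented choice, still less as a justified one.

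**What to change.** In section 2.2, label 36 evaluable (40 recruited) as the FC number only. State that the HS number is matched to it and not derived from this calculation, and that 36 versus 36 detects an FC-HS difference of about 0.67 SD with 80% power at two-sided 0.05. Then choose one of two routes:

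- **(a) Keep noninferiority.** State and justify, before analysis, the margin actually used. Add the matching test to section 2.10.1: the one-sided 95% lower confidence bound for the FC mean CSBM change against 1.8 minus that margin. Describe it as a comparison with a fixed historical figure. The back-calculated 0.5 should not be written in merely because it reproduces 36.
- **(b) Drop noninferiority.** Remove the hypothesis and its 80% power claim. Justify the number by precision (±0.30 CSBM/week at n = 36 and SD 0.89) and by the detectable differences of 0.67 SD between groups and 0.48 SD paired.

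Either route costs wording only and needs no extra patients. The price is that the stated power for the group comparisons becomes less favourable.

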### 2.3. Patients with FC

Patients who match the inclusion criteria will be recruited. FC patients will be diagnosed by two gastroenterologists in the digestion department of the Hospital of CDUTCM, according to the Rome IV Diagnostic Criteria for FC [14]. Each FC patient will undergo a careful physical examination including a routine blood test, routine urine test, routine stool test, blood biochemical test (ALT, AST, BUN, Scr), transabdominal ultrasound, and dynamic electrocardiogram. The inclusion criteria and exclusion criteria of FC patients were as same as our previous study [15].

#### 2.3.1. Inclusion Criteria

Patients will be included in the study if they (1) reach the Rome IV Diagnostic Criteria for FC [14], (2) are right-handers and the age range is between 18 and 35, (3) have less than three CSBMs every week, (4) the Cleveland Constipation Score (CCS) score >10, and (5) provide a written informed consent form.

#### 2.3.2. Exclusion Criteria

Patients will be excluded from the study if they (1) are pregnant women, or plan to be pregnant within 3 months, or are breast-feeding women, (2) are incapable of sports, (3) have a history of head trauma and loss of consciousness, (4) have diabetes or serious cardiovascular, neurological, psychiatric, renal, or respiratory disease, (5) have moderate or serious depression and anxiety, (6) cannot keep silent for 20 minutes while lying down, (7) have any contraindications to fMRI scanning including the presence of metal stent, metal denture, or claustrophobia, (8) have taken other exercises (including meditation and yoga) that may improve constipation over 30 minutes every week in the last 3 months, (9) have taken gastrointestinal motility medicine, nonsteroidal anti-inflammatory medicine, and steroids in the last 15 days, (10) have received other treatments (including surgery, diet modification, biofeedback, or probiotics) in the last month, or (11) have participated in any other clinical trials in the past 3 months.

### 2.4. Healthy Subjects

Those who match the inclusion criteria will be recruited and will receive the same physical examination with the FC patients.

#### 2.4.1. Inclusion Criteria

Subjects will be included if they (1) are right-handers and aged 18–35 years, (2) have no abnormalities during the physical examinations, (3) have passed the National Student Physical Health Standard test, and (4) provide written informed consent.

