#### 2.4.2. Exclusion Criteria

The exclusion criteria for HS are the same as the criteria for FC patients (see Section 2.3.2). Moreover, those who have possible organic diseases, psychological disorders, and gastrointestinal symptoms and signs are also excluded.

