### 2.5. Recruitment Strategy

The participants will be recruited from the Chengdu University of Traditional Chinese Medicine (CDUTCM) by delivering leaflets inside the campus, posting advertisements in billboards, posting at Acupuncture and Brain Science Research Center and CDUTCM (http://cdutcm.edu.cn/) websites, and posting in our WeChat public account.

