#### 2.7.1. General Information Collection

Same as our previous study [15], general information including the demographic data and vital signs will be collected. The demographic data include age, gender, education level, nationality, and body mass index (BMI). The vital signs include body temperature, heart rate, respiratory rate, and blood pressure. Among them, the BMI will be calculated at the baseline and the end of the invention, whereas the vital signs of each patient will be immediately recorded after every training.

According to our hypothesis, the nonspecific effects of Tai Chi include motor function, vital capacity, and psychological state regulation and the specific effects of Tai Chi for FC patients reflects in relieving gastrointestinal symptoms and modulating autonomic nerve function.

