Furthermore, to ensure the reliability and repeatability of the results, we will establish a strict quality control program, which includes the participant selection, the SOP of Tai Chi practice, the SOP of neuroimaging scan, and the outcome measures. For example, for the selection of participants, the freshmen who never practice Tai Chi and have no physical exercise frequently will be taken into consideration. In the implementation of Tai Chi intervention, the SOP of 24-style Tai Chi is established, which covers the requirement on the movements, breathing, and ideas of the participant.

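### The unadjusted FC-versus-HS comparisons are open to confounding by sex and body size, and a fitness test applied to HS alone adds a built-in difference

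*Protocol article*

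**What the plan says.** **Entry.** Section 2.4.1 admits HS who "are right-handers and aged 18–35 years", have a normal examination, "have passed the National Student Physical Health Standard test" and consent. Section 2.3.1 admits FC patients on diagnostic and symptom criteria, and requires that they "are right-handers and the age range is between 18 and 35". It lists no fitness test. Section 2.4.2 states "The exclusion criteria for HS are the same as the criteria for FC patients", with further organic, psychological and gastrointestinal exclusions for HS. Section 2.5 recruits both groups from one university campus by open advertising, and section 3.2 adds that "the freshmen who never practice Tai Chi and have no physical exercise frequently will be taken into consideration". No section describes balancing the groups on sex or BMI.

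**Data.** Section 2.7.1: "The demographic data include age, gender, education level, nationality, and body mass index (BMI".

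**Analysis.** Section 2.10.1: "The clinical data in the two groups (FC group and HS group) will be compared with two-sample" t-tests, with the Mann–Whitney test for non-normal data and paired t-tests within each group. No covariate is named. Section 2.10.2 compares ALFF within each group before and after the intervention, and between FC and HS after the 10 weeks. Section 2.1 draws 15 participants per group at random for MRI.

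**The concern.** The first aim, in the Introduction, is to compare the influence of Tai Chi on motor and respiratory function between FC patients and HS. Disease status defines the groups, so nothing in the design makes them alike in other respects. Isometric leg strength, FEV1, FVC, PEFR and functional reach can be expected to vary with sex and body size, and HRV with sex. If the share of women or the BMI distribution differs between the groups, an unadjusted comparison attributes that difference to constipation.

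The error can go either way. Section 3.1 expects the nonspecific benefits in patients and HS alike, so a composition difference could produce a false contrast against that hypothesis or hide a true one.

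This cannot all be left to a later analysis plan. Who is enrolled is settled at recruitment, and the between-group test is stated rather than left open.

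**Working it through.** The plan gives no figure on this point, so there is nothing of its own to reproduce. The documents supply n = 40 per group (15 for MRI). The rest is assumption.

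**Assumptions.** FVC level; mean sex gap g = 1.2 L; within-sex SD s = 0.6 L (a gap of 2 SD); no true FC–HS difference; 50% women in HS; two-sided 5% test, critical t on 78 degrees of freedom = 1.991.

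**Formulas.** With shares of women p_F and p_H:
- spurious difference B = g(p_F − p_H)
- group variance V = s² + p(1 − p)g²
- standard error used by the t-test = √((V_F + V_H)/40)

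**Variances.** 50% women: 0.36 + 0.25 × 1.44 = 0.7200. 60%: 0.36 + 0.24 × 1.44 = 0.7056. 70%: 0.36 + 0.21 × 1.44 = 0.6624. 80%: 0.36 + 0.16 × 1.44 = 0.5904.

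**Case A: the shares are those of the populations the volunteers come from, so sex varies from sample to sample.** The rejection rate follows from the noncentral t with noncentrality B/SE.

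| Women, FC v HS | B (L) | SE (L) | B/SE | Rejects |
|---|---|---|---|---|
| 60% v 50% | 0.12 | 0.189 | 0.64 | about 10% |
| 70% v 50% | 0.24 | 0.186 | 1.29 | about 25% |
| 80% v 50% | 0.36 | 0.181 | 1.99 | about 50% |

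**Case B: the shares are those actually enrolled.** The difference in means now varies only with the within-sex SD, 0.6 × √(2/40) = 0.134 L, while the test still uses the larger SE.
- 60% v 50%: threshold 1.991 × 0.189 = 0.376 L; (0.376 − 0.12)/0.134 = 1.91; rejects about 3%.
- 70% v 50%: threshold 1.991 × 0.186 = 0.370 L; (0.370 − 0.24)/0.134 = 0.97; rejects about 17%.
- 80% v 50%: threshold 1.991 × 0.181 = 0.360 L; (0.360 − 0.36)/0.134 = 0; rejects about 50%.

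**Smaller gap or smaller sample (Case A, normal approximation; FC 60% / 70% / 80% women).** Gap of 1 SD, n = 40: 6.9% / 12.7% / 23.1%. Gap of 2 SD, n = 15: 6.8% / 12.4% / 23.0%.

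**Chance imbalance.** If both groups come from a source with 50% women, the SD of the difference in share is √(2 × 0.25/n): 11 points at n = 40 and 18 points at n = 15. This is already inside the nominal 5%, but it still shifts the estimate in the one trial that is run.

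**What is not exposed.** A paired before–after test compares each person with himself or herself, so fixed differences in sex or size cancel. They do not cancel in a between-group comparison of levels after practice, which is how section 2.10.2 (for ALFF) and the Discussion read.

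**The case against.** **Age.** A reader might infer that the 18–35 band leaves the groups unmatched on age. The documents do not support that as a main concern: the band is the same in both groups, both come from one campus, and freshmen are singled out. The shared source and exclusions are partial controls. Sex and BMI remain.

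**Certainty.** A reader might infer that the comparisons are confounded. No sex split is given, so only the risk is established. At 60% versus 50% women enrolled, the test in the illustration rejects in about 3% of trials, below nominal.

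**Change scores.** The first aim can be read as a comparison of change, which would remove fixed level differences. That has force, but the article does not say that changes are compared between groups. Change would also not remove a difference in response by sex or body size.

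**Reach.** The illustration covers FVC level only. It should not be carried over to the Berg scale, timed up-and-go, FEV1/FVC or the questionnaires, where the body-size argument is weaker.

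**Scope.** Covariates are often left to an analysis plan, so their absence from an article alone would be weak evidence. Here the unadjusted test is stated, and matching is a recruitment matter.

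**Conclusion.** The point holds as a conditional risk. With no balancing on sex or BMI described and an unadjusted between-group test stated, the FC–HS comparisons of leg strength, FEV1, FVC, PEFR, functional reach, HRV and ALFF can pick up group composition. Under an assumed 2-SD sex gap in FVC level and n = 40 per group, the false-positive rate is about 17–25% at 70% versus 50% women and about 50% at 80% versus 50%. The lower end of the first range takes the shares as enrolled, the upper end as population shares. Smaller gaps or imbalances give less, and the true imbalance is unknown.

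One asymmetry needs no assumption about volunteers: only HS must pass the student fitness test. This selects one group on fitness in a trial that compares motor and respiratory outcomes, and neither matching nor adjustment on sex and BMI removes it. The documents do not allow its size to be estimated.

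**What to change.** 1. **Section 2.10.1.** Replace the between-group t-test with ANCOVA of the end-of-intervention value on group, baseline value, sex, baseline BMI and age. All are already collected, so the cost is close to nil. Because the groups are not randomised, ANCOVA and an analysis of change can disagree if baseline means differ, so the covariate-adjusted change should be reported alongside.
2. **Section 2.10.2.** Compare the change in ALFF between groups, with sex and age as covariates. This costs two of the 28 degrees of freedom (15 + 15 − 2).
3. **Sections 2.4.1 and 2.1.** Where still feasible, frequency-match the HS not yet enrolled to the FC group on sex and BMI band, and stratify the remaining MRI draw by sex. The Abstract reports 20 HS and 18 FC patients enrolled, leaving 40 − 20 = 20 HS to match. Matching will be imperfect: the first 20 HS are unmatched, 40 − 18 = 22 FC patients are still to come, and some baseline scans may be done. Some HS volunteers would be turned away.
4. **Sections 2.3.1 and 2.4.1.** Make the fitness criterion the same in both groups. For participants already enrolled the difference cannot be undone, so it should be reported as a limitation.
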